### Sample size

Based on an estimated rate of two severe asthma exacerbations per participant over the 12-month period in the placebo group, a minimum of 222 participants (111 per group) will be required to provide 80 % power (at 5 % two-sided significance level) to detect a clinically meaningful 25 % reduction in the average exacerbation rate in the group using the TLA device.

This sample size is based on a Poisson regression model, with the treatment group as the covariate and a 10 % overall dropout rate. A review of comparative interventions of proven efficacy in severe asthma gave effect sizes ranging from 21 to 63 %, with a mean of 41 %. Given that this is a pragmatic trial where we expect our intervention to be less effective than an efficacy trial, we have chosen a deliberately more conservative effect size of 25 %. This represents on average, one less severe exacerbation every 2 years.

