### Clinical outcomes analysis

The primary statistical analysis will be carried out on the basis of intention-to-treat (ITT). The primary efficacy endpoint in this study, the rate of clinically significant exacerbations over the 12-month period, will be analysed using a Poisson regression model to compare the rate of asthma exacerbations between the two groups with log of time used as an offset variable. Further analysis will adjust for the baseline characteristics including the ACQ score, age, body mass index (BMI) and sex.

Continuous secondary endpoints which involve repeated measures at baseline, 3, 6, 9, and 12 months (including measures of lung function, composite asthma control scores and health-related quality-of-life measures) will be analysed using longitudinal analysis methods, including mixed effect models to determine any effect of the TLA device over time. Continuous variables with only baseline and 12 months data, (including lung function and carer quality of life measures) will be analysed by analysis of covariance (ANCOVA) of the 12-month outcome adjusted where appropriate for baseline, minimisation factors and other important factors as detailed for the primary outcome.

Kaplan–Meier curves and log-rank test will be used to compare the time to first asthma exacerbation between the two groups. Cox proportional hazards models will be used to evaluate the effect of TLA device on the time to first asthma exacerbation, adjusting for the same covariates as in the primary analysis. Since the analysis of only time to first exacerbation leaves out much of the data, analysis incorporating multiple time-to-event (recurrent exacerbations) methods will also be used, including the Andersen–Gill extension.

The proportion of participants experiencing severe exacerbations over the 12-month follow-up period will be compared using a continuity-corrected Chi-squared test. The duration of severe exacerbations, the total number of days in an exacerbation state over the 12-month follow-up period, and the number of health care utilisations will be compared between the two groups using two-sample independent t-tests.

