### Missing data

We will attempt to minimize the missing data due to item non-response during the long follow-up period by ensuring timely contact with the participants and robust follow-up procedures. The expected participant’s dropout has already been factored into the sample size calculation. Missing data will be reported with reasons given where available, and the missing data pattern, explored. In order to be consistent with the ITT, missing data for the primary endpoint will be imputed using multiple imputation (MI) techniques. Our imputation model will be sufficiently general to include all the baseline variables thought to be important predictors of the response indicator of each target variable to be imputed. This will improve the validity of the imputation model under the missing at random (MAR) assumption on which the MI is based. In addition, an ignorable likelihood-based analysis will be applied for the mixed effect models.

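### Total exacerbation days and healthcare-use counts are compared by t-tests that ignore follow-up time, so the comparison is biased if follow-up differs by arm

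*Protocol article*

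**What the plan says.** The last paragraph on between-group tests in the protocol article's Clinical outcomes analysis section puts three secondary endpoints under one method. It names "The duration of severe exacerbations, the total number of days in an exacerbation state over the 12-month follow-up period", and then adds that "the number of health care utilisations will be compared between the two groups using two-sample independent t-tests". No exposure term, covariate or clustering term is attached to any of the three.

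The same section treats the exacerbation count differently. The primary Poisson model is fitted "with log of time used as an offset variable", and for the timing of exacerbations "analysis incorporating multiple time-to-event (recurrent exacerbations) methods will also be used, including the Andersen–Gill extension".

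The Sample size section allows for attrition: the calculation is made "with the treatment group as the covariate and a 10 % overall dropout rate". The split of that dropout between arms is not given. The Missing data section says that "missing data for the primary endpoint will be imputed using multiple imputation (MI) techniques" and applies an ignorable-likelihood approach to the mixed models. Neither provision reaches the t-test endpoints.

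**The concern.** Days in exacerbation and number of healthcare contacts accumulate with time under observation. Someone who leaves at six months has had half the opportunity to accrue either. A t-test on raw totals gives that person's total the same standing as a full-year total. The plan recognises the issue for the primary count, where the offset corrects for it, but not for two endpoints of the same kind.

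If one arm is followed for less time on average, its totals are lower for that reason alone, and the difference is read as a treatment effect or hides one. These endpoints would support statements about exacerbation burden and resource use.

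Duration raises a separate question. It is measured once per exacerbation, and the protocol expects several per person: the calculation is "Based on an estimated rate of two severe asthma exacerbations per participant over the 12-month period in the placebo group". The article does not say whether the unit of analysis is the event or the participant. An independent-samples test is wrong if it is the event.

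**Working it through.** **Inputs from the protocol article.** 111 per group; placebo rate 2.0 per year; "clinically meaningful 25 % reduction in the average exacerbation rate", so 1.5 per year on the device; 80 % power; two-sided 5 %; 10 % overall dropout.

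**Reproducing the stated 222.** One Poisson-regression formula gives n per arm = [1.960·√(2/2) + 0.842·√(1/2 + 1/1.5)]² / (ln 0.75)² = 99.46. Dividing by 0.90 gives 110.5, rounded up to 111 per arm, or 222. (A Wald formula on the log rate ratio gives 110.6 before any dropout. Nothing below depends on which was used.) The article gives no figure for the t-test endpoints, so their behaviour has to be worked out.

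**Assumptions not in the article.** A healthcare-use count with mean 2 per year; gamma frailty variance k between 0 and 1; dropout times uniform over the year and unrelated to event rate; no imputation; several splits of dropout by arm.

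**Bias in the ratio of mean totals.** With dropout proportion d, mean follow-up is 1 − d/2 years.
- 10 % in both arms: 0.95/0.95 = 1.00, no bias.
- 15 % control, 5 % device: 0.975/0.925 = 1.054 under no effect. A true 0.75 reads as 0.75 × 0.975/0.925 = 0.79.
- 5 % control, 15 % device: 0.925/0.975 = 0.949 under no effect. A true 0.75 reads as 0.75 × 0.925/0.975 = 0.71.
- 20 % control, none on device: 1.00/0.90 = 1.11 under no effect.

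**Type I error of the t-test.** The variance of a total is 2·E(T) + 4·[(1 + k)·E(T²) − E(T)²], with E(T) = 1 − d/2 and E(T²) = 1 − 2d/3. For the 15 %/5 % split:
- k = 0.5: variances 3.83 and 3.95; SE = √(7.775/111) = 0.265. The spurious difference is 2 × (0.975 − 0.925) = 0.10, or 0.38 SE. Rejection probability is 6.7 % by this approximation and 6.3 % in 20,000 simulated trials.
- k = 1: variances 5.63 and 5.88; SE = 0.322; shift 0.31 SE; 6.1 %.
- k = 0: SE = 0.191; shift 0.52 SE; 8.2 % (8.1 % simulated).

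For the extreme 20 %/0 % split, simulated error is 18.5 % at k = 0 and 12.0 % at k = 0.5. With 10 % in both arms it is 5.1 %, 4.8 % and 5.1 % at k = 0, 0.5 and 1.

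**Does an offset cure it?** In every split tried under no effect, the rate ratio with a log-time offset is 1.00. A plain Poisson Wald test is not a safe replacement, however: its type I error is about 16 % at k = 0.5 and 25 % at k = 1. The variance must allow for overdispersion.

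**Duration.** Simulation with 111 per arm and mean 2 events, within-person correlation (ICC) assumed:

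| ICC | t-test on events | t-test on participant means |
|---|---|---|
| 0 | 4.8–4.9 % | 5.1–5.3 % |
| 0.1 | 7.1–7.9 % | 4.4–4.7 % |
| 0.3 | 12–17 % | 4.7–5.5 % |
| 0.5 | 17–21 % | 5.0–5.3 % |

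Ranges span k = 0 and k = 0.5. On either unit, people with no exacerbation contribute nothing. At rates 2.0 and 1.5 the event-free share is e⁻² = 14 % against e⁻¹·⁵ = 22 % with k = 0, or 2⁻² = 25 % against 1.75⁻² = 33 % with k = 0.5. The subset compared is therefore itself affected by treatment.

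**The case against.** The strongest defence is that the protocol gives no reason to expect unequal dropout. Its only figure is 10 % overall, and with equal loss the t-test on totals is valid, overdispersed or not. That stands, and it makes the concern conditional.

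A reader might infer that the t-tests generally exaggerate these results. The documents do not support that: the direction depends on which arm loses more, and with heavier loss on placebo a real benefit is understated.

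A reader might also infer that all three tests ignore repeated events within a person. That is wrong for total days and utilisation, which are one sum per participant. It could apply to duration, but only if events are the unit, which the article does not say. One value per participant is at least as natural a reading of a two-sample test, and an article may leave the unit to the fuller plan.

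Healthcare use is also to be collected from patient records (Measurement of secondary outcomes), so some utilisation after departure may be recovered. This softens the point for that endpoint, but how leavers enter the totals is not stated.

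Finally, the offset assumes that leaving is unrelated to event rate; if it is related, the rate model is biased too. That limits the remedy, but does not argue for raw totals.

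**Conclusion.** The point holds in a conditional form. For total exacerbation days and healthcare-use counts, the article fixes a method with no allowance for follow-up time, at odds with its own handling of the primary count and with its expectation of dropout. The bias is zero if follow-up is equal. It is about 5 % in the ratio at a 15 %/5 % split and 11 % at 20 %/0 %, in either direction. These sizes rest on the assumed split and on uniform, uninformative dropout times; the type I error rates rest also on the assumed mean and dispersion.

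For duration, inflated error of about 7–21 % (ICC 0.1 to 0.5) arises only if exacerbations are treated as independent observations. The article does not establish that they will be. What holds on any reading is that the comparison is restricted to those who exacerbated.

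The primary analysis, the sample size and the separately specified economic evaluation are untouched.

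**What to change.** - **Total days and healthcare utilisations:** model both with log follow-up time as an offset and report rate ratios with confidence intervals. Use negative binomial regression or Poisson with robust variance for utilisation. Use robust variance for days, which accrue in multi-day blocks. Keep the arm means in the tables.
- **Follow-up time:** define it for each endpoint, including whether records review extends it for those who leave, and report it by arm.
- **Duration:** state the unit, either one value per participant or a per-event model clustered on participant. Label the result descriptive, since neither choice removes the selection on having exacerbated.

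The cost is a change of analysis wording before unblinding, using data already being collected. The one downside is that rate ratios replace mean differences as the main contrast.

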### Missing data

We will attempt to minimize the missing data due to item non-response during the long follow-up period by ensuring timely contact with the participants and robust follow-up procedures. The expected participant’s dropout has already been factored into the sample size calculation. Missing data will be reported with reasons given where available, and the missing data pattern, explored. In order to be consistent with the ITT, missing data for the primary endpoint will be imputed using multiple imputation (MI) techniques. Our imputation model will be sufficiently general to include all the baseline variables thought to be important predictors of the response indicator of each target variable to be imputed. This will improve the validity of the imputation model under the missing at random (MAR) assumption on which the MI is based. In addition, an ignorable likelihood-based analysis will be applied for the mixed effect models.

### Interim analysis and criteria for early study termination

No interim analysis is planned; however, the DSMC will perform regular reviews of all study outcome and adverse event data to ensure that there is no difference in rates of hospitalisation or exacerbation in either group. The DSMC will determine final criteria for early study termination, which may be based on clear-cut evidence of worsened safety in one of the trial arms, and in the case of evidence beyond reasonable doubt of clear-cut benefit in the primary outcome measure, an effect size which would change clinical practice in the presence of the current literature and understanding of the disease area.

### Economic evaluation

The perspective adopted in the economic evaluation will be that of the National Health Service (NHS) and social services; therefore, productivity losses and over-the-counter medication costs will not be included in the base case analysis. However, in a sensitivity analysis, we will assess the impact of including these costs on the cost-effectiveness results.

A within-trial cost-utility analysis will explore the incremental cost per QALY gained by TLA usage when compared to sham-TLA usage. Cost and effect results will be reported as means with standard deviations, with mean differences between the two patient groups reported alongside 95 % confidence intervals (CI). Incremental cost-effectiveness will be calculated by dividing the difference in costs by the difference in effects. Uncertainty around the incremental cost-effectiveness ratio (ICER) will be explored using non-parametric bootstrapping [29].

Building on the results of the trial and subsequent cost-effectiveness analysis, a Markov model will be constructed to determine the costs and outcomes, over the life-time of the patient, of TLA usage. The model structure will be informed by results from this trial, and from previously published studies, with experts within the team advising on the final structure of the model. The analysis will determine the cost per life year gained and cost per QALY gained when nocturnal TLA treatment is compared to placebo. The model will be run over the patient lifetime, with costs and benefits discounted at a rate of 3.5 %. Probabilistic sensitivity analyses will be conducted to deal with uncertainty in model parameters and cost-acceptability curves presented, [30] and will be extended to consider the application of value of information (VoI) techniques, which are included in economic evaluations to inform policy decisions about the value of further research.

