### Measurement of secondary outcomes

Outcomes reflecting current asthma control will be measured in the clinic at 3, 6, 9 and 12 months, and will include (i) measures of lung function (pre-bronchodilator FEV_1_, mean morning pre-bronchodilator peak expiratory flow (PEF) rate over 2 weeks prior to the visit, fractional concentration of exhaled nitric oxide (F_E_NO)); (ii) measures of the risk of future adverse asthma outcomes (severe exacerbations, systemic corticosteroid use over the 12 months, post-bronchodilator FEV_1_ at 12 months); (iii) symptom control patient-reported scores Asthma Control Questionnaire (ACQ), Asthma Control Diary, and Sino-Nasal Outcome Test (SNOT-22) score; and (iv) health-related quality of life for both the study participant (standardised asthma quality of life questionnaire (AQLQ(S)) and EuroQol 5-dimension 5-level questionnaire (EQ5D-5L) and the carer (Adult Carers Quality-of-Life questionnaire (AC-QoL) at 12 months only). Responses to the EQ-5D will be converted into utilities using UK population tariffs [26] and combined with survival information to generate quality-adjusted life years (QALYs). A global evaluation of treatment effect (GETE score) will be recorded at 12 months.

The usage of the device will be measured from participant reports at 3, 6, 9 and 12 months and also by an engineer at the time of device filter change at 6 and 12 months.

We will assess the costs associated with the TLA device (including acquisition, installation and servicing). In addition, using patient questionnaires and review of patients’ records, health and social care resource use data will be collected. Resource use data will be valued using NHS and social care costs schedules [27]. Work productivity and activity impairment (WPAI) questionnaires will be given to the participant (WPAI - Asthma) at 3, 6, 9 and 12 months, and to the carer (WPAI – Care Giver) if applicable at 12 months.

Thematic analysis of qualitative data will elicit information on the participant and their partner’s perception of the treatment device.

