At the second visit (Randomisation Visit 2), the asthma control diary and peak flow diary is collected. Participants complete the following questionnaires: ACQ, AQLQ, EQ-5D-5L, WPAI-A, SNOT-22 and the LASER Indoor Air Quality Questionnaire. Pre-bronchodilator spirometry is performed, and FENO is measured. Allergy testing is performed if this was not possible at Screening Visit 1. Participants are issued with the following: (i) a LASER diary for daily recording of overnight device use (hours,) additional device use (hours,) time off work as a result of asthma (hours) and dose of oral corticosteroids (mg); (ii) exacerbation diary cards for completion at the onset of an exacerbation throughout the trial (including PEF, steroid dose, reliever medication use and nocturnal wakening); and (iii) an Asthma Control Diary for completion prior to their next follow-up visit (including morning pre-bronchodilator PEF.) Participants will also be issued a Resource Use Log and a participant identification card.

Participants whose partner and/or carer wish to participate in the trial are asked to attend together for either visit 1 or visit 2 so that Carer/Partner consent can be obtained. Partners are asked to consent for participation in the qualitative study and carers are asked to consent to completion of questionnaires at visit 2 and at the 12-month follow-up visit (ACQoL and WPAI-CG).

One month following the Randomisation Visit 2, participants are contacted by telephone for their 1-month telephone review, where device delivery and installation will be confirmed, and any problems with the device or trial can be addressed.

Follow-up visits are held at 3-, 6-, 9- and 12-months post-randomisation. Participants collect 2 weeks of peak flow recordings and an asthma control diary prior to each follow-up visit. At the follow-up visits, participants complete questionnaires (ACQ, AQLQ, EQ-5D-5L, SNOT-22 and WPAI-A) and perform pre-bronchodilator spirometry and FENO. At each follow-up visit, exacerbation history is reviewed along with self-reported device usage using the LASER diary and healthcare resource use log. Device reported use is also documented at each follow-up visit.

At the 12-month follow-up visit, a GETE questionnaire will also be completed.

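### Read literally, the within-trial QALY difference is not adjusted for the baseline EQ-5D-5L utility already collected; adjusting it would be a free improvement to the ICER

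*Protocol article*

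**What the plan says.** The Economic evaluation section of the protocol article sets out the within-trial cost-utility analysis in sequence. First, "Cost and effect results will be reported as means with standard deviations, with mean differences between the two patient groups" are given, with 95% confidence intervals. Then: "Incremental cost-effectiveness will be calculated by dividing the difference in costs by the difference in effects". Uncertainty around that ratio "will be explored using non-parametric bootstrapping". No covariate or regression model for QALYs appears in the sequence.

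The baseline measurement exists. At Randomisation Visit 2, according to the Study visit schedule section, "Participants complete the following questionnaires: ACQ, AQLQ, EQ-5D-5L, WPAI-A, SNOT-22 and the LASER Indoor Air Quality Questionnaire". EQ-5D-5L is repeated at 3, 6, 9 and 12 months. The section on measurement of secondary outcomes says that utilities are combined with survival to form QALYs, and does not mention the baseline value.

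Two other places bear on the point. The minimisation factors under Randomisation and blinding are site, prevalent or incident case, previous exacerbations, oral corticosteroid use and FEV1; utility is not among them. The Clinical outcomes analysis section does plan baseline adjustment (ANCOVA) for continuous outcomes measured only at baseline and 12 months, and mixed models for repeated measures that include baseline.

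**The concern.** Baseline utility usually predicts later utilities well. If QALYs are computed as an area under the utility curve, it also enters the QALY directly as the first point. An unadjusted QALY difference therefore contains, besides the treatment effect, a share of whatever baseline difference arose by chance. The design does not balance utility directly, so only chance and its correlation with the minimisation factors keep the arms alike.

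At stake are the realised QALY difference, which is the denominator of the ICER, and the width of the interval around it. A ratio with a small denominator is sensitive to small shifts in that denominator. The measurement needed to remove the shift is already in the data.

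**Working it through.** **Plan's own figures.** The article states no figure for the QALY difference, utility SD or correlation, so there is none to reproduce on this point. The sample size supplies the number per arm. The Poisson-regression formula with a 1:1 binary covariate, rates 2.0 and 1.5, 80% power and 5% two-sided alpha gives 198.9, so 199. Allowing 10% dropout, 199 / 0.9 = 221.1, so 222, or 111 per arm, as stated. After 10% dropout about 100 per arm remain (111 × 0.9 = 99.9).

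**Assumed inputs (not in the article).** Baseline utility SD 0.20 to 0.30; slope of 12-month QALY on baseline utility 0.5 to 0.7; correlation of baseline utility with QALY 0.5 to 0.7.

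**Step 1: identity.** Unadjusted difference = adjusted difference + slope × baseline imbalance.

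**Step 2: size of a chance imbalance.** Standard error of the baseline difference = SD × √(2/n).
- Low end: 0.20 × √(2/111) = 0.0268.
- High end: 0.30 × √(2/100) = 0.0424.

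**Step 3: shift in the QALY difference for a one-standard-error imbalance.**
- Low end: 0.5 × 0.0268 = 0.0134.
- High end: 0.7 × 0.0424 = 0.0297.

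The shift is about 0.013 to 0.030 QALY, in either direction.

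**Step 4: interval width.** Ratio of adjusted to unadjusted width = √(1 − r²).
- r = 0.5: 0.87, so 13% narrower.
- r = 0.7: 0.71, so 29% narrower.

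**Step 5: cross-check by a different route.** Assume a trapezoid QALY with weights 0.125, 0.25, 0.25, 0.25 and 0.125 at 0, 3, 6, 9 and 12 months, and equal correlation rho between any two utilities. The slope is then 0.125 + 0.875 × rho, which is 0.475 at rho 0.4 and 0.825 at rho 0.8. With SD 0.15 to 0.30 and 111 per arm, a one-standard-error imbalance shifts the QALY difference by 0.010 to 0.033. At SD 0.25 the standard error falls from 0.0245 to 0.0186 (24%) at rho 0.4, and from 0.0308 to 0.0136 (56%) at rho 0.8. The range in Step 4 is therefore not generous to adjustment.

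**Step 6: illustration on the ICER scale.** Take the cost difference as the article's £2,088 annual rental alone, ignoring any savings, and assume a true gain of 0.05 QALY. Then 2,088 / 0.05 = £41,760 per QALY. A shift of +0.02 gives 2,088 / 0.07 = £29,829; a shift of −0.02 gives 2,088 / 0.03 = £69,600. With an assumed gain of 0.10 the figures are £20,880, £17,400 (2,088 / 0.12) and £26,100 (2,088 / 0.08). These show sensitivity only and do not forecast the trial's ICER.

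**The case against.** The strongest objection is that the article never calls the differences crude or unadjusted. A regression-adjusted difference is also a difference in means, and the quoted ICER sentence is a definition that holds for adjusted increments too. A journal article condenses a fuller protocol, and QALY covariates are detail often left to an analysis plan. The contrast with the Clinical outcomes analysis section is suggestive, but that section does not cover the economic analysis. Its mixed models for quality of life may well use EQ-5D-5L with its baseline, although nothing says that this feeds the ICER. This objection stands as a limit on confidence. It does not remove the point, because the article gives a working sequence which, followed as written, yields an unadjusted QALY difference, and a better estimator is available from data already collected.

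Three stronger readings are tempting and are not supported:
- **That the ICER is biased.** Under randomisation the unadjusted QALY difference is unbiased on average, and the planned confidence intervals and bootstrap carry chance imbalance as sampling uncertainty. What is lost is precision and the accuracy of the realised estimate given the imbalance seen. Minimisation on factors related to utility may also make imbalances somewhat smaller than Step 2 implies.
- **That costs are distorted in the same way.** The argument concerns QALYs. The article offers no mechanism or figure by which leaving out baseline utility would distort the cost difference.
- **That the lifetime model inherits the problem.** The article says the model structure draws on trial results and published studies; it does not say that the within-trial QALY difference is an input.

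The area-under-the-curve form of the QALY is likewise an assumption here.

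**Conclusion.** The point holds as a free improvement, with moderate confidence. As written, the within-trial QALY difference has no adjustment for baseline utility. This is not a systematic error. It leaves the point ICER exposed to a measured and removable chance imbalance: about 0.013 to 0.030 QALY per standard error of imbalance, if the utility SD is 0.20 to 0.30, the slope 0.5 to 0.7 and there are 100 to 111 participants per arm. It also forgoes an interval about 13% to 29% narrower, if the baseline-to-QALY correlation is 0.5 to 0.7. None of the SDs, slopes or correlations comes from the article, so the sizes are ranges under assumption. If an analysis plan that is not shown already specifies the adjustment, the remaining task is to align the article's wording with it.

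**What to change.** State in the economic evaluation section or the analysis plan, before unblinding, that:
- incremental QALYs are estimated by regressing the 12-month QALY on treatment arm, baseline EQ-5D-5L utility and the minimisation factors;
- that adjusted difference is the denominator of the ICER and is re-estimated in every bootstrap resample;
- the unadjusted arm means, SDs and difference are kept as a descriptive table.

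The cost is a few lines of text and a regression inside the bootstrap loop. It needs no new data, visits or participants. Fixing it in advance also rules out a later choice between an adjusted and an unadjusted ICER.
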